- Detainees or recently released ex-detainees who meet the eligibility criteria will be offered the opportunity to participate in the study. Participation will be voluntary. Detainees who do not meet eligibility criteria or choose not to participate will return to their previous location as determined by the security staff. The standard of care for HIV discharge will not be affected by their refusal to participate.
- Detainees or recently released ex-detainees who elect to participate will complete written, informed consent for study participation with the study research assistant (RA). The informed consent form will be read aloud to the participant (see Appendix D: Informed Consent Forms). A copy of the informed consent will be provided to the participant. For participants recruited inside the DC DOC facilities, the GWU RA will provide the option of leaving their copy with the RA in order to protect confidentiality and receiving it at their next study visit after being released to the community. The RA will maintain a file of completed informed consents at the administrative study office at the Department of Epi/Bio at GWU in a locked file cabinet.
- Consenting study participants will also be asked to provide consent for release of medical records from the DC DOC facilities and any community medical providers that they may come into contact with during the course of the study.
- A study locator form requesting contact information for participants after release in the community will be completed. In the case of recently released ex-detainees the locator form will include participants’ current and anticipated contact information.

For community-recruited individuals, the baseline visit will occur within one study visit as much as possible. However, for individuals recruited inside correctional facilities, the baseline visit may be split across multiple time points if necessary, as determined by constraints of that facility.

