***Monthly contact by phone/in-person***

1. To enhance retention in the study, study staff will conduct monthly check-in phone calls or visits with all study participants to update locator and contact information and provide an opportunity for individuals in the texting intervention group to customize the frequency and content of their text message for the next month (including reminders for the next medical appointment, ART dosing, and prevention plan goal). In addition, participants will be asked about HIV medication adherence for that past month (See Appendix N: Monthly call Script and Medication Adherence Tool) to help validate self-reported adherence at the 12-week and 24-week in-person assessments. Study staff will also remind study participants about the next monthly call date and next study appointment date. A $10 incentive in the form of an American Express Gift Cheque will be provided for each successful monthly contact, and participants can opt to receive the incentive at that visit (if in person), arrange for another date/time for pick-up (if by phone), or receive their bundled incentives at the next study visit.

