4. At the end of the study visit the staff will provide a list of referrals, a $50 incentive for completion of the visit, $10 incentives for every successful monthly phone call since the previous study visit, and a voucher for transportation. The incentives will be in the form of American Express Gift Cheques.
5. After the study visit, the study staff will confirm the participant’s engagement in care by contacting his/her medical provider and obtaining data on appointments, plasma viral load, CD4 data if available and antiretroviral medication prescriptions, given approved medical release from the participant.

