**Re-incarceration Plan:**

Correctional facility rosters will be reviewed to track re-incarceration throughout the study period, allowing the study team to locate participants who are re-incarcerated as well as determine time individual participants spend incarcerated during the follow-up period.  Should a participant be re-incarcerated or put under supervision within a correctional facility at the time a 12 or 24 week assessment visit (Study Visits 2 or 3) is due, the assessment visit will be conducted within the correctional facility if possible.  The following exceptions will be made to the standard follow-up assessment visits for those conducted within the correctional setting:

1) Blood will not be drawn for plasma vial load assessment.  Instead, the correctional facility medical record will be reviewed for a HIV PVL result within two weeks of the assessment visit.

2) No incentive or transportation vouchers will be provided for completing assessment visits while incarcerated.  The participant will have the option of picking up the $50 incentive (in the form of an American Express Gift Cheque) at the GWU study office if released prior to the completion of the funding period.

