The longitudinal nature of the study (containing a baseline assessment before intervention and two follow-up visits after jail release) will result in repeated assessments of primary outcomes (plasma viral load suppression at Visits 2 and 3) and secondary outcomes (e.g., proportion linking to community HIV care at 30 days, 60 days, 90 days, etc.). These outcomes will be analyzed in the unified framework of generalized linear models (GLMs) with appropriate link functions (logit for dichotomized outcomes, e.g. linkage to care, detectable PVL; identify link for continuous outcomes, e.g. log-transformed PVL; or log link for count outcomes, e.g. # of non-main sexual partners). The setup of GLMs involves relating the expected outcome to a linear function of explanatory covariates, where the explanatory covariates will include a dummy variable encoding the treatment (=1) versus control (=0), dummies for study site and gender, relevant demographic covariates, and their interactions. Depending on the analysis objectives, three GLM model structures will potentially be used: 1) *Marginal models* will be used to analyze population-level intervention effect. Within-individual correlation of repeated measures will be accounted for using Generalized Estimating Equations (GEE),^6,7^ which yields consistent parameter estimates and robust standard error estimates. 2) *Random-effect generalized linear models* will be used to estimate the intervention effect at the individual-level.^8^ For those outcomes with only one follow-up visit, the model will be estimated using conditional logistic regression for binary outcomes or difference-on-difference regression for continuous outcomes for better estimation efficiencies. 3) *Markov transition models* will be used to investigate the intervention effect on the individual behavior change as previously conducted by this group,^9^ and includes the prior history of the outcomes as regression covariates; therefore, the transition model emphasizes more the effect of the intervention on outcome changes given the prior value of the outcome. Using these model setups, we will examine the different aspects of intervention for SA2 and SA3. These models will also allow us to quantify the differences between the two study sites and differences between male and female by testing the interaction between study arm and site, and potentially the interaction between study arm and gender.

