*Strategy of handling missing data:* Differential LTF between arms could eliminate the randomization effect. The first round of analyses will make the “missing at random” (MAR) assumption, which states that after conditional on baseline covariates, there is no systematic difference between those LTF and those retained in the study. With the MAR assumption, we will construct logistic regression models that express “missingness” as a function of covariates, and use the logistic model to calculate the propensity score for “missingness” for each individual. We will use the propensity score in terms of inverse probability weighting to adjust for the selection bias due to missing data in our regression analysis.^10^ Afterwards, we will relax the MAR assumption by conducting a sensitivity analysis through considering a family of plausible “not missing at random” models using the techniques outlined by Diggle and Kenward^11^ and Daniels et al.^12^

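### The first-round missing-data analysis takes loss to be ignorable given baseline covariates, and does not name the collected follow-up data that may predict loss for the weights

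*Protocol*

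**What the plan says.** The Analysis Plan names as repeated endpoints the "primary outcomes (plasma viral load suppression at Visits 2 and 3"; its marginal model for the population-level effect is fitted by GEE.

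For missing data, the first round of analyses assumes that "after conditional on baseline covariates, there is no systematic difference between those LTF and those retained in the study". Under that assumption, missingness is modelled by logistic regression "as a function of covariates, and use the logistic model to calculate the propensity score", and the score is used for "inverse probability weighting to adjust for the selection bias due to missing data in our regression analysis". The assumption is then relaxed in a sensitivity analysis over a family of not-missing-at-random models. Loss is also compared by Pearson's chi-square test to examine whether it induces selection bias.

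Elsewhere the Protocol collects follow-up data that bear on loss. Facility rosters track re-incarceration and time in custody (Re-incarceration Plan). At monthly contacts "participants will be asked about HIV medication adherence for that past month". Viral load is measured at Visit 2. None of these is named as an input to the missingness model.

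**The concern.** Weights built on baseline covariates remove selection bias only if, given those covariates, dropping out is unrelated to what happens during follow-up. That is a strong assumption here. Someone who is unsuppressed at Visit 2, back in custody or reporting poor adherence may be more or less likely to give a Visit 3 viral load, and those facts also bear on suppression at Visit 3. The intervention may change them too, so the selection can differ by arm.

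GEE does not repair this by itself. When loss depends on earlier outcomes, it is not generally consistent unless the weights reflect that dependence. Loss explained by recorded data can be corrected under a missing-at-random assumption, provided the assumption conditions on those data. The stated one does not.

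A second weakness concerns the baseline data. Participants recruited in custody are randomised at baseline visit 2, but their baseline blood draw and community interview come at the post-release visit. Anyone not seen after release lacks those covariates, so baseline weights are thinnest for a group exposed to loss.

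**Working it through.** The Protocol states no expected retention, effect size or power, so there is no plan figure to reproduce. What follows is an illustration, and **every rate in it is assumed**. It shows one mechanism: missingness that runs through re-incarceration, for a single-visit risk difference.

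**Inputs (assumed).** Suppression if not re-incarcerated is 50% in control and 60% in intervention. Suppression if re-incarcerated is 30% or 70%, the same in both arms. Viral load is missing for 15% of those not re-incarcerated and 31%, 69% or 85% of those re-incarcerated. Re-incarceration, control v intervention, is 30% v 30%, 40% v 25% or 40% v 20%. Baseline covariates are taken not to predict re-incarceration, so baseline weights leave the arm means as observed. If they do predict it, the bias is smaller.

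**Formulas, per arm.** With r the re-incarceration rate, sN and sR suppression without and with re-incarceration, and mN and mR the matching missing fractions:

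- True = (1-r)·sN + r·sR
- Retained = (1-r)(1-mN) + r(1-mR)
- Observed = [(1-r)(1-mN)·sN + r(1-mR)·sR] / Retained

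**Upper end** (r 40% v 20%, sR 70%, mR 85%):

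- Control: true 0.6×0.5 + 0.4×0.7 = 0.580; observed (0.255 + 0.042)/0.57 = 0.521
- Intervention: true 0.8×0.6 + 0.2×0.7 = 0.620; observed (0.408 + 0.021)/0.71 = 0.604
- True difference 4.0 points, estimated 8.3, bias +4.3

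**Lower end** (same, but sR 30%):

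- Control: true 0.420; observed (0.255 + 0.018)/0.57 = 0.479
- Intervention: true 0.540; observed (0.408 + 0.009)/0.71 = 0.587
- True difference 12.0 points, estimated 10.8, bias -1.2

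**Selected cases, in percentage points:**

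| Re-incarcerated, control v intervention | sR | mR | Retained | True | Estimated | Bias |
|---|---|---|---|---|---|---|
| 40% v 20% | 70% | 85% | 57% v 71% | 4.0 | 8.3 | +4.3 |
| 30% v 30% | 30% | 85% | 64% v 64% | 7.0 | 9.3 | +2.3 |
| 40% v 20% | 70% | 31% | 79% v 82% | 4.0 | 4.7 | +0.7 |
| 40% v 25% | 30% | 85% | 57% v 67% | 10.5 | 10.4 | -0.1 |
| 40% v 20% | 30% | 85% | 57% v 71% | 12.0 | 10.8 | -1.2 |

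**With arm and re-incarceration in the weights.** In the upper-end control arm, the retained masses 0.51 and 0.06 are weighted by 1/0.85 and 1/0.15. They return to 0.60 and 0.40, and the mean is again 0.580. The same holds in the other arm, so the bias is zero. This is by construction, because missingness was assumed to depend on nothing else.

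**The chi-square test.** In the second row retention is identical in the two arms (0.7×0.85 + 0.3×0.15 = 0.64), yet the estimate is off by 2.3 points. A test of loss rates by arm has nothing to detect there.

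**Precision.** With 75 per arm, the upper-end case leaves 75×0.40×0.15 = 4.5 re-incarcerated participants with a value in control and 75×0.20×0.15 = 2.25 in intervention, each with weight 1/0.15 = 6.7. Where bias is largest, its removal rests on few people.

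**The case against.** The strongest reply is that the plan does not stop at the first round: it commits to not-missing-at-random models. A reader might infer that informative loss goes uncorrected altogether, and the Protocol does not support that. The gap concerns the weighted missing-at-random estimate. Sensitivity models probe what cannot be seen, whereas the predictors at issue here are recorded.

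Next, the weight-model sentence says only covariates; the word baseline stands in the definition of the assumption. The transition models use prior outcomes, and random-effect models fitted by likelihood to both visits can accommodate loss that depends on an observed Visit 2 result. The choice of weight variables is also commonly left to a statistical analysis plan. All this is fair, and baseline-only weights are an inference, though the natural one because the weights are built under that assumption. The other model types address individual-level or transition effects. The assumption is fixed in the Protocol itself, so its wording can be criticised there.

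Three further readings are tempting and do not hold:

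- **Window.** For participants in custody, "the correctional facility medical record will be reviewed for a HIV PVL result within two weeks of the assessment visit". It may look as if they get two weeks while others get eight. These are different quantities: the eight weeks is the distance of the visit from its target, and still applies to custody visits; the two weeks is the distance of the chart value from that visit.
- **Provider records.** Engagement in care is confirmed after the visit "by contacting his/her medical provider and obtaining data on appointments, plasma viral load, CD4 data if available and antiretroviral medication prescriptions". The text does not exclude people who miss the visit, and the enrolment release already covers "any community medical providers that they may come into contact with during the course of the study".
- **Direction.** Nothing shows that the re-incarcerated are the least likely to be suppressed. The Background says that release harms adherence, so suppression in custody could be higher.

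Finally, a rich weight model with many arm interactions could be unstable at this sample size. That stands, and it limits the fix.

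**Conclusion.** The point holds in a limited form. The first-round assumption conditions on less than the trial observes, and the weights follow from it. If loss depends on arm, Visit 2 viral load, re-incarceration or adherence, the weighted GEE estimate can carry bias that recorded data could remove. The documents settle neither how large it would be nor which way it would run. The range of -1.2 to +4.3 points rests wholly on assumed rates and on baseline covariates not predicting re-incarceration. It applies to a single-visit risk difference, not to the planned repeated-measures logit model. This is a worthwhile improvement to the stated method and does not show that the planned analysis is invalid.

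**What to change.** 1. Restate the missing-at-random assumption as conditional on the observed history up to each visit: arm, pre-randomisation covariates, earlier viral load and recorded follow-up data.
2. Use visit-specific weights in a weighted GEE. Take them from a parsimonious missingness model with arm, pre-randomisation covariates, the previous viral load result and roster-tracked re-incarceration, plus monthly adherence where available. Say how missing predictors are handled, since adherence and Visit 2 results may be absent for the same people.
3. Add arm interactions only where the data support them. Stabilise or truncate the weights by a rule set in advance, and report their distribution.
4. Keep the chi-square comparison of loss as description, and do not read a non-significant result as evidence that selection bias is absent.
5. Keep the not-missing-at-random models as a further step.

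Optionally, as a sensitivity analysis only, use correctional-chart or provider viral loads falling within the visit window when the study value is missing. These may come from other laboratories than the one that tests study specimens.

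Steps 1 to 5 change analysis wording and use data already planned, with no added visits or blood draws. The price is somewhat more variable weights, hence a less precise estimate, with at most 150 participants. The optional analysis may need some extra chart abstraction.

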**Study Timeline:**

Up to 150 participants will be enrolled in the study. Recruitment will begin in August 2013 for 18-24 months, and follow-up visits will conclude in August 2015. Data analysis and dissemination will commence soon after the first follow-up visit and will continue through to the end of the study (June 2015).

| **Activity** | **Time frame** |
| --- | --- |
| IRB submission | June 2012 |
| IRB approval | September 2012 |
| Recruitment | August 2013 – February 2015 |
| Follow-up visits (12 and 24 weeks) | November 2013 – August 2015 |
| Data analysis and dissemination | August 2013 – June 2016 (with no cost-extension) |

